#### Soil-transmitted helminth infection

Stool samples will be collected in rounds 2 and 4 from all household members in a randomly selected subset of 500 households and used to assess the presence and intensity of soil-transmitted helminth (STH) infection. Formalin ether concentration and microscopy will be used to quantify worms and ova for hookworms, *Ascaris lumbricoides*, and *Tricuris trichura.*^53^ Quality assurance includes independent duplicate assessment of all positive and 10% of negative samples. After stool collection, each participant will be offered a single dose of Albendazole, a broad-spectrum antihelmenthic drug recommended by the Ministry of Health and Family Welfare, Government of India. Stools collected in round 2 will allow for comparison of STH infection prevalence between intervention and control villages, while the stool samples collected ∼8 months later in round 4 will provide a measure of re-infection rate.

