### Study design

This study uses a matched cohort design to assess the effectiveness of a completed intervention with data collected across four study rounds from June 2015 to October 2016 (figure 2). Data were collected in all study rounds for diarrhoea, acute respiratory infection, nutritional status and stored and source water outcomes to assess seasonality. Data were collected in rounds 2 and 4 for EED, seroconversion, and hand-rinses, and cross-sectionally in one or more rounds for the remaining outcomes. As described below, control villages were matched to randomly selected intervention villages through a multistep restriction, genetic matching and exclusion process using the following eligibility criteria.

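### The round-4 stool samples cannot measure helminth re-infection, because infection that persisted after the offered dose cannot be told apart from infection acquired again

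*Protocol article*

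**What the plan says.** Everything specific to this outcome stands in the protocol article, under Outcome measurement, Soil-transmitted helminth infection.

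- **Sampling:** "Stool samples will be collected in rounds 2 and 4 from all household members in a randomly selected subset of 500 households". The samples are "used to assess the presence and intensity of soil-transmitted helminth (STH) infection".
- **Treatment:** "After stool collection, each participant will be offered a single dose of Albendazole". The text does not say whether intake is observed or recorded.
- **Role of round 2:** "Stools collected in round 2 will allow for comparison of STH infection prevalence between intervention and control villages".
- **Role of round 4:** the samples taken about 8 months after the first set "in round 4 will provide a measure of re-infection rate". This is the only purpose given for the second helminth sample.

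No stool between the dose and round 4 is described anywhere in the article. The Statistical analyses section covers health outcomes with multilevel regression in general terms. It gives no numerator or risk set for re-infection.

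**The concern.** Re-infection presupposes an earlier infection that was cleared. To observe it, one needs to know that a person was infected, then free of infection, then infected again. The schedule supplies the first and third facts but not the second. Someone positive at both rounds may have declined the dose, may have taken it without clearing, or may have cleared and been infected again.

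This is more than a definition left to a fuller document. The article makes a positive statement about what the schedule will deliver, and no later choice of numerator or denominator can recover clearance from stools at rounds 2 and 4 alone.

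What is at stake is the reading of a secondary outcome. A re-infection rate would be taken as evidence on transmission after treatment. If much of it is persistent infection, a real intervention effect on transmission may be hidden.

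**Working it through.** **Stated figures.** The article gives no re-infection figure to reproduce. Only the interval can be checked. The Study design section has "data collected across four study rounds from June 2015 to October 2016", which is 17 months. 17 / 4 = 4.25 months per round, and two rounds are 8.5 months, consistent with the stated interval of about 8 months.

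**Inputs.** None of the following is in the documents; all are assumptions shown over a range.
- p = round-2 prevalence
- k = uptake × cure: 1.0 × 0.9 = 0.90, 0.9 × 0.8 = 0.72, 0.8 × 0.5 = 0.40
- r = risk of infection up to round 4 in persons free of infection after round 2

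Round-4 positives as a share of everyone sampled are the sum of three parts:
- uncleared: p(1 − k)
- true re-infection: p·k·r
- new infection in round-2 negatives: (1 − p)·r

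**Step 1: round-2 positives only.** The uncleared share of their round-4 positives is (1 − k) / [(1 − k) + k·r].

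| k | r = 0.10 | r = 0.30 |
|---|---|---|
| 0.90 | 0.10 / 0.19 = 53% | 0.10 / 0.37 = 27% |
| 0.72 | 0.28 / 0.352 = 80% | 0.28 / 0.496 = 56% |
| 0.40 | 0.60 / 0.64 = 94% | 0.60 / 0.72 = 83% |

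With complete uptake and cure (k = 1) the share is 0%.

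**Step 2: effect on a true difference, same risk set.** Take r = 0.20 in control and 0.14 in intervention villages (true ratio 0.70), with k equal in both groups. The observed ratio is [(1 − k) + 0.14k] / [(1 − k) + 0.20k].
- k = 0.90: 0.226 / 0.280 = 0.81
- k = 0.72: 0.3808 / 0.424 = 0.90
- k = 0.40: 0.656 / 0.680 = 0.97

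**Step 3: if every round-4 positive were counted.** Take the same r = 0.20 in both groups and p = 0.20 (control) v 0.15 (intervention). Prevalence in round 4 is r + p(1 − k)(1 − r).
- k = 0.50: 0.260 / 0.280 = 0.93
- k = 0.70: 0.236 / 0.248 = 0.95
- k = 0.90: 0.212 / 0.216 = 0.98

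Here carry-over alone gives an apparent difference of 2% to 7%. Step 3 can be avoided, because round-2 results identify who was negative then. The mixing in step 1 cannot be undone with the samples collected.

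**The case against.** The article says that the samples provide a measure of re-infection. It does not say that round-4 prevalence is that measure, and it fixes no numerator. The risk set and the handling of dose acceptance may stand in a fuller plan that is not shown. Silence on observed or recorded intake does not show that intake goes unrecorded. All of this stands, and it rules out two stronger readings.

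- **A reader might infer that first infections will be counted as re-infections.** The text neither states nor forces this. It points to one subset of households tested at both rounds, so round-2 negatives can be set apart.
- **A reader might infer that the study would report a false effect, for example a 25% reduction.** That figure arises only if there is no transmission at all after round 2 and every round-4 positive is counted: with prevalences of 20% and 15% in round 2, clearance cancels and 15% / 20% = 0.75 remains. The documents state neither condition. With round-2 positives as the denominator and equal uptake and cure, the same scenario leaves equal proportions positive in both groups and a ratio of 1.00. In that risk set, persistence pulls a true effect toward the null and does not create one.

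It is also fair to say that the outcome is secondary, and that neither the diarrhoea outcome nor the round-2 helminth comparison depends on this wording.

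The objection does not reach the central point. Among round-2 positives, no unseen definition can separate persistence from re-infection on this schedule.

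**Conclusion.** The point holds in a limited form. The article attributes to the round-4 stool a property that its schedule does not give. Among persons positive in round 2, the round-4 result measures persistent infection and re-infection together.

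Under the assumed values, the uncleared share ranges from 27% to 94%, and a true ratio of 0.70 appears as 0.81 to 0.97. If uptake and cure were nearly complete, the problem would be small, but nothing described in the article would show that. The dilution result assumes equal uptake × cure in intervention and control villages; if these differed, the observed ratio could move in either direction.

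The consequence is a mislabelled secondary outcome that would support a weaker claim about transmission than its name suggests. It is worth correcting because the correction is cheap.

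**What to change.** - Describe the round-4 outcome as infection prevalence and intensity about 8 months after treatment was offered, and drop the term re-infection rate.
- Use new infection in round 4 among persons negative in round 2, by species and study arm, as the transmission measure.
- Report round-2 positives who are positive again as 'persistent or re-infected', broken down by dose acceptance where that was recorded. State that the two cannot be separated.

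**Cost.** The change is one of wording and analysis, with no further stool sample and no change to treatment. The incidence analysis loses the round-2 positives and anyone not sampled in round 2, so its risk set is smaller. It also relies on the round-2 negatives being true negatives. The article describes duplicate reading for all positive samples but only 10% of negative ones, so that limit should be stated with the result.

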#### Environmental enteric dysfunction

Stools from a randomly selected subset of 200 children <2 years old, collected in rounds 2 and 4, will be used to assess EED through quantification of biomarkers of intestinal inflammation and permeability. Fecal myeloperoxidase (MPO), α-1-antitrypsin (AAT), and neopterin (NEO), markers for neutrophil activity, intestinal permeability and TH1 immune activation, respectively, were selected for this study based on evidence of association with EED, subsequent linear growth deficits and household environmental fecal contamination.^24^
^25^
^54^

#### Seroconversion for enteric pathogens

Serological assays that assess antibody production against various enteric pathogens can provide an objective measure of exposure to enteric infections.^55^ Enrolling children aged 6–18 months will reduce the potential for interference from maternally acquired antibodies and permit analysis of seroconversion data in a critical window for young children who experience higher diarrhoeal disease morbidity and mortality before 2 years of age.^56–61^ Children who are 6–12 months during round 2 will have capillary blood drawn by fingerstick or heelstick, as appropriate, and will be visited again during round 4 for a second capillary blood sample. All blood samples will be preserved on TropBio (Sydney, Australia) filter discs and stored within 7 days of collection at −20°C. Seroconversion against markers for norovirus, *Giardia intestinalis*, *Cryptosporidium parvum*, *Entamoeba histolytica*, enterotoxigenic *Escherichia coli*, heat-labile enterotoxin (ETEC-LT), *Salmonella* spp., *Campylobacter jejuni*, *Vibrio cholerae* and *Toxoplasma* spp. will be assessed using multiplex immunoassay technology on the Luminex xMAP platform.^62^

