**Trial registration number:**

NCT02441699.

Strengths and limitations of this studyThe study assesses a combined household-level piped water and sanitation intervention that requires complete community-level compliance.The intervention was not randomly allocated; but, controls are selected through a restriction process to limit possible partial exposure to the intervention through spill over, and matched to intervention villages using preintervention data.The study uses a holistic definition of health to assess intervention impacts on physical, mental and social well-being, including more novel outcomes such as seroconversion to enteric pathogens, environmental enteric dysfunction and sanitation insecurity. It also assesses intervention coverage, cost-effectiveness and collective efficacy.The time lapse between intervention completion and the beginning of the evaluation process prevents baseline comparison or assessment of immediate intervention impacts. However, it allows for a biologically plausible length of time for die-off of even the most persistent pathogens in the environment and provides time for children to have been born into this environment.

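### Serology is named only as seroconversion from round 2 to round 4, so any arm difference built up before round 2 falls outside the outcome

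*Protocol article*

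**What the plan says.** The section on seroconversion for enteric pathogens sets a paired design. "Children who are 6–12 months during round 2 will have capillary blood drawn by fingerstick or heelstick", and the same children "will be visited again during round 4 for a second capillary blood sample". Seroconversion against a panel of markers "will be assessed using multiplex immunoassay technology on the Luminex xMAP platform". The study design section repeats the schedule: "Data were collected in rounds 2 and 4 for EED, seroconversion, and hand-rinses". The abstract and the study aims also name seroconversion and no other serology outcome.

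The gap between the two rounds is given in the section on soil-transmitted helminths, where the second stool is collected about "8 months later in round 4". That section plans two uses of its samples: prevalence in round 2 is compared between intervention and control villages, and the stools collected 8 "months later in round 4 will provide a measure of re-infection rate". No round 2 comparison is stated for serology.

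The strengths and limitations box says that the delay after completion rules out a baseline comparison but "provides time for children to have been born into this environment". The village eligibility section puts the start of the Motivation phase in 2002–2006, with a roll-out of about 3 years on average. Data collection ran from June 2015.

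**The concern.** In a trial with a true baseline, counting only new conversions after the first sample loses nothing that belongs to the intervention. Here the first sample is taken in children who have lived 6–12 months in an intervention or control village. If the intervention reduces exposure, the arms should already differ in round 2. Conversion from round 2 to round 4 leaves that difference out.

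It also conditions on a post-exposure variable. Among round 2 negatives, the children most readily infected have already left the risk set, and more of them have left in the control arm.

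The article presents serology as an objective measure of enteric exposure. The primary outcome is reported diarrhoea, which it describes as open to bias, and its discussion says field workers may know village status while laboratory staff are blinded. A serology contrast that is imprecise or pulled towards the null is a weaker check on the primary result than the collected samples allow.

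**Working it through.** The article gives no seroprevalence, infection rate, sample size or power for serology, so it has no serology figure to reproduce. The interval can be checked: "data collected across four study rounds from June 2015 to October 2016" is 17 months, and 17/4 × 2 = 8.5 months for two evenly spaced rounds, in line with about 8.

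**Inputs**
- From the article: age 6–12 months in round 2; gap D = 8 months.
- Assumed: ages uniform over 6–12 months; constant hazard λ of 0.02–0.15 per month in controls; hazard ratio 0.80 (the article's effect size of 0.20 is for diarrhoea and is only borrowed here); risk from birth, or from 3 or 6 months of age. Antibody waning and village clustering are not modelled.

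**Formulas**, with a = months at risk before round 2
- Positive in round 2: 1 − exp(−λa)
- Conversion among round 2 negatives: 1 − exp(−λD)
- Conversion over all sampled children: exp(−λa) × (1 − exp(−λD))
- Information on log λ from a binary result with cumulative hazard H: I(H) = H² exp(−H) / (1 − exp(−H))
- Gain from using both samples: [I(λa) + exp(−λa) I(λD)] / [exp(−λa) I(λD)]
- With gamma frailty of variance v, survival is (1 + vλt)^(−1/v) in place of exp(−λt).

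**Worked case**: a = 9, λ = 0.10 in controls and 0.08 in intervention
- Positive in round 2: 1 − exp(−0.90) = 59.3% v 1 − exp(−0.72) = 51.3%. This difference of 8.0 points is outside the named outcome.
- Conversion among negatives: 1 − exp(−0.80) = 55.1% v 1 − exp(−0.64) = 47.3%. The hazard ratio is 0.64/0.80 = 0.80, unbiased. The risk ratio is 0.86.
- Conversion over all children: 0.407 × 0.551 = 22.4% v 0.487 × 0.473 = 23.0%, ratio 1.03.
- Information: I(0.90) = 0.555; 0.407 × I(0.80) = 0.212; gain (0.555 + 0.212)/0.212 = 3.6.
- Frailty variance 1, negatives only: ln(2.36/1.72) / ln(2.70/1.90) = 0.316/0.351 = 0.90.

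**Averaged over ages 6–12 months, risk from birth** (gain at the control rate)

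| λ | Positive in round 2, control v intervention | HR among negatives, homogeneous | HR among negatives, frailty variance 1 | Conversion over all children (ratio) | Information gain |
|---|---|---|---|---|---|
| 0.02 | 16% v 13% | 0.80 | 0.83 | 12.4% v 10.4% (0.84) | 2.3 |
| 0.05 | 36% v 30% | 0.80 | 0.87 | 21.1% v 19.2% (0.91) | 2.7 |
| 0.10 | 59% v 51% | 0.80 | 0.90 | 22.7% v 23.2% (1.02) | 3.5 |
| 0.15 | 73% v 65% | 0.80 | 0.92 | 18.7% v 21.4% (1.14) | 4.8 |

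On the log hazard ratio, with both arms combined, the gains are 2.3, 2.6, 3.3 and 4.4.

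**Sensitivity to the start of risk**
- From 6 months, the gain is 1.4–1.8 over the same hazards. The all-children ratio reaches only 0.96 at 0.15 per month, so nothing reverses.
- From 3 months, the all-children ratio is 0.96 at 0.10 per month and 1.05 at 0.15.

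**Sensitivity to frailty**: from birth at 0.10 per month, variance 0.25 gives 0.84 among negatives instead of 0.90.

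The added analyses reduce the frailty attenuation but do not remove it. In the worked case with variance 1, the round 2 contrast on the cumulative hazard scale is ln(1.72)/ln(1.90) = 0.542/0.642 = 0.84, against 0.90 among negatives.

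**The case against.** Paired conversion is a legitimate measure of incidence. The article gives a reason for its age window: less interference from maternal antibody, and coverage of a critical period before age 2. Leaving early infections out follows from that choice. Maternal antibody also tells against relying on round 2 positivity. Mothers live in the same villages, so residual maternal antibody could be more common in control infants and flatter the intervention, an error that conversion among negatives avoids. This stands, and it is why the added analyses should supplement seroconversion and not replace it.

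A reader might infer that the round 2 results are thrown away. The article does not say so: the blood is collected and assayed, and nothing excludes comparing it by arm. The definition of seroconversion and its at-risk set may be in a full protocol or SAP, and their absence from an article is no fault.

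A reader might also infer that the planned outcome will show a reversed effect. That needs conversions divided by all sampled children, a denominator the article never states, and about half or more of the children already positive in round 2, a figure it does not give. Among round 2 negatives no reversal occurs under any frailty examined. Nor is it settled that a child positive in round 2 cannot convert; under a fold-rise definition such a child could.

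What survives is narrower. The outcome that is named excludes the round 2 arm difference, and the article's own helminth plan shows that such a contrast was considered feasible.

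**Conclusion.** The point holds as a loss of information and a possible attenuation in a secondary outcome. Round 2 is not a baseline, and the only named serology outcome starts from it. Under the assumptions above, adding the round 2 result gives about 2.3–4.8 times the information per child with risk from birth and about 1.4–1.8 times with risk from 6 months. The gain is largest for common pathogens. Among round 2 negatives, a true hazard ratio of 0.80 is estimated without bias if children are homogeneous, and as 0.83–0.92 with frailty variance 1 and risk from birth. Counting over all sampled children would weaken the contrast further, and could reverse it only where about half or more are already positive in round 2.

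The hazards, hazard ratio, frailty variance and start of risk are all assumed. The gains are upper figures to the extent that round 2 positivity reflects maternal antibody, or that village clustering limits precision.

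**What to change.** Keep seroconversion, name round 2 negatives as its at-risk set, and label the result as conditional on being negative in round 2. Beside it, add:

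1. an age-adjusted comparison of round 2 seroprevalence by arm, for each pathogen;
2. a supporting joint analysis of both samples, with positive in round 2 left-censored at that age, negative then positive interval-censored, and negative twice right-censored, using a complementary log-log model with a village random effect;
3. a sensitivity analysis that excludes the youngest children who were positive in round 2.

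The children, visits and assays are unchanged. The cost is some extra analysis and wording. The remaining weakness is that round 2 positivity may partly reflect maternal antibody, possibly to a different degree in each arm, and the report should say so.

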#### Environmental fecal contamination

Field workers will collect samples of household stored drinking water and source water from a random subset of 500 households in all four rounds, and child hand rinses in rounds 2 and 4. All water and hand rinse samples will be stored on ice during transport and analysed within 6 hours of collection using membrane filtration. Three assays will be used: (1) plating on m-Coli Blue 24 (Millipore, Billerica, Massachusetts, USA) for *E. coli* according to EPA Method 10 029, (2) alkaline peptone water enrichment prior to plating on thiosulfate citrate bile salts sucrose agar and slide agglutination serotyping for *V. cholerae* and (3) plating on xylose lysine desoxycholate agar, and slide agglutination serotyping for *Shigella* spp.^63–65^ Source and stored water samples will be assayed for *E. coli*, *V. cholerae* and *Shigella* spp., and hand rinse samples will be assayed for *E. coli* and *Shigella* spp. *E. coli* was selected as a standard non-human specific indicator of fecal contamination, though the limitations of this indicator are well-established.^66–68^ In order to better characterise human fecal contamination of the household environment, *V. cholerae* and *Shigella* spp. were selected based on prevalence in southern Asia, evidence of public health importance, and field laboratory limitations.^69–71^

#### Cost and cost-effectiveness

Costs and potential cost savings (ie, averted costs) associated with the intervention will be assessed through an economic costing approach that recognises and quantifies costs and benefits from a societal perspective.^72^ Data on programme and point-of-delivery inputs will be collected at household, community and implementer levels in round 3. Field workers will administer community surveys to a village leader, and household surveys to the household decision-maker for toilet installation, in 20 randomly selected households in 20 matched intervention and control villages. Given cost-effectiveness analyses require the effect of the intervention to be measured against a counterfactual, and the intervention of interest is a community-based intervention, cost and effectiveness measures will be summarised at the village level.^73^ Surveys will collect data on household-level and community-level inputs related to materials and labour required to construct household toilets and wash rooms, the community water tank and distribution system and household water connections; longer-term water supply and toilet maintenance costs and financing required for this infrastructure as well as perceived benefits, including averted social opportunity costs. Implementer inputs from Gram Vikas will be collected through an enumeration exercise, interviews and examination of the implementer's financial records.

